### Mediation and Moderation

For outcomes where statistically significant differences in acceptability, appropriateness, and feasibility are observed (ie, significant regression coefficients for the treatment variable associated with the participant-level intercept or slope growth factors), post hoc analysis will examine the roles of substance use and technology use as potential mediators. A primary assumption is that uTECH will be associated with improvement in awareness of how technology influences engagement in HIV risk and substance use behavior [78-80]. For each mediator, validated substance use and technology reports will be entered into the model. Like the approach described for primary outcomes, we will specify latent growth curve factors for the hypothesized mediators to understand the covariation of observations within individuals across time. Subsequently, we will examine whether initial differences in the mediators or changes in the mediators over time account for associations between the outcome variable and the treatment conditions. We will use strategies for assessing time-varying mediators that permit regression coefficients of the outcome on the mediator to vary over time. Where appropriate, we will examine the utility of applying these techniques. We will use parameter constraint approaches [81] to assess the statistical significance of indirect pathways. Bootstrapping [82] tests of mediation cannot be conducted with latent variable mediators and nonnormal exogenous variables. When appropriate, we will use alternative approaches such as Bayesian structural equation modeling and Monte Carlo simulation methods in the presence of nonnormality and complex latent variable structures [83]. Participant-level reports of substance use and technology use will be entered into the models, and we will examine whether initial levels of substance use and technology use (or changes in these variables over time) moderate the association between primary outcome variables and treatment condition by examining the significance of interaction terms between growth factors.

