### This Study

We hypothesize that the uTECH+YMHP intervention will be considered acceptable, appropriate, and feasible by most participants. Furthermore, we hypothesize that participants receiving the combined uTECH+YMHP intervention will show greater and more sustained reductions in substance use and sexual risk behaviors compared to those receiving the YMHP intervention alone. Specifically, we anticipate that the integration of ML-informed SMS text messages will enhance the efficacy of YMHP counseling methods by providing personalized, timely, and contextually relevant support, ultimately leading to improved health outcomes in this sample of SGM young adults.

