### Planned Analytic Approach

Primary outcomes for the study include the acceptability, appropriateness, and feasibility of each intervention condition. In addition, we will examine behavioral health outcomes (sexual risk and protective behaviors and substance use) in both intervention conditions. Tests of fixed effects for estimates of time-specific differences will be performed using appropriate contrasts. Trend changes and their significance will be analyzed, driven by variance components (random effects). We will use growth curve modeling [75] to examine the effects of treatment on outcomes. Growth curve factors also account for the covariation of follow-up observations within participants. Data from 3-, 6-, 9-, and 12-month follow-up assessments will be modeled using latent growth factors using R statistical software [76] (version 4.4.0; R Foundation for Statistical Computing). Because the first nonbaseline time point in the latent growth curve will be the 3-month follow-up, significant differences in the intercept factor would indicate significant postintervention effects. Significant differences in slope factors would indicate that the groups follow different trajectories. When this is noted, potential group differences at each follow-up assessment will be evaluated by varying the location of the referent time point.

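### Moderation is to be tested on growth factors of substance use and technology use that, on the plain reading, are post-randomisation, so the interactions cannot be read as subgroup effects

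*Protocol article*

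**What the plan says.** - **Growth factors.** Planned Analytic Approach: "Data from 3-, 6-, 9-, and 12-month follow-up assessments will be modeled using latent growth factors". The intercept sits at the first of these visits ("Because the first nonbaseline time point in the latent growth curve will be the 3-month follow-up"), and the article reads a group difference in it as an effect seen after the intervention.
- **Mediators.** Mediation and Moderation: where treatment differences are significant, "post hoc analysis will examine the roles of substance use and technology use as potential mediators". Their modelling follows the same pattern: "Like the approach described for primary outcomes, we will specify latent growth curve factors for the hypothesized mediators".
- **Moderators.** The same section then asks "whether initial levels of substance use and technology use (or changes in these variables over time) moderate the association between primary outcome variables" (the other side of that association being trial arm). The test proceeds "by examining the significance of interaction terms between growth factors".
- **Aim.** This Study expects the combined condition to show "greater and more sustained reductions in substance use and sexual risk behaviors" than counselling alone.
- **Baseline data.** Baseline Interview lists substance use among its topics. Missing Data gives baseline data a supporting role; its examples are balance, attrition and covariate control. Moderation is not among them.

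**The concern.** A moderator should be fixed before treatment can act on it. Randomisation then balances it, and a treatment-by-moderator term compares treatment effects across kinds of participant. Here the moderators appear to be estimated from visits at which treatment has already had time to act, and one of them is a variable the trial sets out to change. The same two variables would also serve both as consequences of treatment (mediators) and as conditions on its effect (moderators). A significant term could then reflect how treatment altered substance use, with no difference in effect between heavier and lighter users at entry. At stake is any statement about who finds the text-message component more acceptable, appropriate or feasible.

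**Working it through.** **1. Timing.** YMHP Scheduling and YMHP Sessions put the four counselling sessions at week 1, week 2, month 1 and month 2. The uTECH Intervention section plans 100 messages over 12 months, so about 100 × 3/12 = 25 by month 3. At the 3-month intercept all counselling is due to be complete and about a quarter of the messages sent. A slope over months 3 to 12 lies wholly after randomisation.

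**2. Reading of the test.** Treatment condition is not itself a growth factor. I read the stated interaction as treatment multiplied by the moderator's intercept or slope factor, in a model for the outcome's growth factors.

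**3. Why the interaction can be biased.** Let U be an unmeasured cause of the outcome Y with variance 1, and T the treatment indicator. Let Y = τT + bU + error, with no moderation. Let the 3-month moderator be M = (a − kT)U + noise of variance s². The slope of Y on M is
- control: ab/(a² + s²)
- treated: (a − k)b/((a − k)² + s²)

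These generally differ when k ≠ 0, so the T × M term is non-zero although treatment works equally for everyone. In simulation with no true moderation (4000 replicates, nominal 5% test), the 3-month moderator was significant in 5.2% of runs when treatment left this link alone, 5.9% at an intermediate setting and 10.5% when treatment halved it. The baseline moderator stayed at 4.8-5.5%.

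**4. Power, as illustration.** There is no stated figure to reproduce: Sample Size Calculation and Power Analysis covers only the acceptability main effect. Its autocorrelations of 0.1 and 0.5 belong to acceptability and cannot be carried over to substance use or technology use.

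Assume that baseline use is the true modifier, that the baseline test has 80% power (two-sided 5%), and that the baseline-to-3-month correlation is r. The noncentrality with the baseline moderator is 1.960 + 0.842 = 2.802. With the 3-month moderator it is about 2.802r, and power ≈ Φ(2.802r − 1.960), plus a small opposite tail.

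| r | Formula | Simulation, n = 313 | Simulation, n = 301 |
|---|---|---|---|
| 0.1 | 6% | 6% | – |
| 0.5 | 29% | 25-26% | 25% |
| 0.7 | 50% | 44-45% | 43% |
| 0.9 | 71% | 68-69% | – |

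Here 313 is about 95% of 330, and 301 is the number the Results section reports as completing 12 months. The simulations fall slightly lower because the part of the baseline effect that the 3-month score does not carry goes into residual error. By the formula, power falls below 40%, half of 80%, only when r < (1.960 − 0.253)/2.802 ≈ 0.61.

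**5. Reversed assumption.** If the 3-month level is the true modifier, the 3-month test has 79% power and the baseline test 25% (r = 0.5) or 45% (r = 0.7).

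Both simulations use one observed 3-month score in a linear model, not a four-wave latent factor.

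**The case against.** **Initial levels may mean baseline.** The moderation sentence names no visit, it speaks of entering participant-level reports, the phrase "Because the first nonbaseline time point in the latent growth curve will be the 3-month follow-up" could imply that a baseline point exists, and the baseline examples under Missing Data are not exhaustive. This stands as a real ambiguity. It does not rescue the plan: the only test named uses growth factors, the only ones described begin at 3 months, and the change factors are post-randomisation however the first phrase is read.

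**Technology use is not clearly a target.** This also stands. The article expects better awareness of how technology influences behaviour, not less use. The argument is firmest for substance use, although both variables are named as mediators.

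**The analysis is secondary.** True. The section opens as post hoc work, and no primary estimate or sample size depends on it. That limits the importance without making the specification sound.

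**Tempting stronger readings.** A reader might infer that the analysis loses most of its power. The documents do not support that: they give no moderation power and no correlation for these variables, more than half is lost only if r is below about 0.61 and baseline use is the modifier, and the ranking reverses otherwise. A reader might also treat the sentence "Bootstrapping [82] tests of mediation cannot be conducted with latent variable mediators and nonnormal exogenous variables" as part of this defect. It is too absolute, since participants can be resampled and the model refitted. But it is a separate, minor matter, and the section already names usable alternatives (parameter constraints, Bayesian structural equation modelling and Monte Carlo methods).

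**Conclusion.** The point holds as one of bias and interpretation. Followed as written, the moderation analysis would condition the treatment effect on post-randomisation quantities, at least one of which the trial intends to change, and the result could not be presented as a subgroup effect. The size of the bias cannot be derived from the documents. The doubling of false positives, from about 5% to 10%, belongs to one constructed scenario and shows only that the problem can matter. The power figures are illustrative, because they rest on an assumed correlation, an assumed starting power of 80% and an assumed baseline modifier. Importance is modest because the analysis is secondary and post hoc.

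**What to change.** In Mediation and Moderation:

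1. Define the moderators as baseline values: substance use from the baseline interview, and a named baseline technology-use measure. The Table 2 item on sites and apps used to meet partners is a candidate.
2. Test treatment × baseline value on the outcome's intercept and slope factors.
3. Delete the parenthesis on change over time from "whether initial levels of substance use and technology use (or changes in these variables over time) moderate the association between primary outcome variables", and delete the clause "by examining the significance of interaction terms between growth factors".
4. State that post-baseline levels and change in these variables are used for mediation only.

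No change to the bootstrap sentence is required for this point.

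The cost is model-specification wording, with two checks. Table 2 does not say which item is asked at which visit, so collection of the technology item at baseline needs confirming. It is also only a proxy: eligibility already requires recent dating-app use, so a graded or count version would separate participants better than a yes/no one. Because the Results section says that analysis is under way, the change should be dated and recorded before any moderation result is seen.

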### Sample Size Calculation and Power Analysis

For the power calculation, we used 1 primary outcome, acceptability. We used a balanced repeated measures design [84] with pretreatment baseline measurements. Using a logistic regression generalized linear mixed model [85], we allowed an individual’s 5 measurements (baseline and 3-, 6-, 9-, and 12-month) for acceptability to be correlated via an autoregressive-1 structure. With an initial sample size of 330 (to account for 95% retention), an autocorrelation of 0.1, and a baseline effectiveness of 85%, we aimed to detect a minimum time-averaged difference of 9% in acceptability between any 2 conditions, maintaining 80% power and an a priori α level of .05. This calculation was based on pairwise comparisons between uTECH+YMHP versus YMHP-only conditions. If the autocorrelation [86] between measures within the same individual was as high as 0.5, the sample size was adjusted to detect a minimum difference of 11% between the 2 conditions. A 9% to 11% difference between the 2 conditions is considered statistically significant, given the existing evidence supporting YMHP and the relative cost-effectiveness and ease of delivery of the uTECH intervention. The ability to demonstrate a small increase in the acceptability of uTECH over YMHP will support the widespread implementation of uTECH in future efficacy trials.

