**Primary**					
	Acceptability, appropriateness, and feasibility of uTECH SMS text messages	Adapted from AIM^a^, IAM^b^, and FIM^c^ [65]		5-item Likert scale	
	Acceptability, appropriateness, and feasibility of Young Men’s Health Project	Adapted from AIM, IAM, and FIM [65]		5-item Likert scale	

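### The stated 80% power refers to a time-averaged yes/no acceptability outcome in a logistic mixed model and does not apply to the growth-model tests the protocol describes

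*Protocol article*

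**What the plan says.** Sample Size Calculation and Power Analysis covers one of the three primary outcomes: "For the power calculation, we used 1 primary outcome, acceptability". The model is stated as "Using a logistic regression generalized linear mixed model [85"], which takes a binary response. It allows five "measurements (baseline and 3-, 6-, 9-, and 12-month) for acceptability to be correlated via an autoregressive-1 structure". The inputs are given as "With an initial sample size of 330 (to account for 95% retention), an autocorrelation of 0.1, and a baseline effectiveness of 85" percent, and the target is that "we aimed to detect a minimum time-averaged difference of 9% in acceptability between any 2 conditions", with 80% power at an alpha of .05. At an autocorrelation of 0.5 the target becomes 11 points.

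The analysis sections describe something else.

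- Table 2 lists the measure for every primary outcome as "5-item Likert scale", adapted from three implementation scales. No threshold for calling a participant accepting is given.
- Primary Outcomes places these assessments at 3, 6, 9 and 12 months, with none at baseline.
- Planned Analytic Approach says "Data from 3-, 6-, 9-, and 12-month follow-up assessments will be modeled using latent growth factors". It reads a group difference in the intercept (located at 3 months) as a post-intervention effect and a difference in slope as differing trajectories. It also mentions fixed-effect contrasts for time-specific differences.
- Mediation and Moderation defines a significant difference in the primary outcomes as a significant treatment coefficient on the intercept or slope growth factor.

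**The concern.** A power statement is useful only if it refers to the test on which the conclusion will rest. Here it and the described analysis differ in response scale, set of measurements, model and contrast. A reader told that the trial had 80% power for 9 points could not use that figure to interpret a null 3-month intercept or a null slope.

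The choice of contrast matters in itself. A time average pools all visits. An intercept at the first follow-up leans mainly on one end of the series, and a slope test does not respond at all to a difference that is constant over time, which is the simplest form of the effect that was powered.

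**Working it through.** **1. The plan's own figure.** Inputs from Sample Size Calculation and Power Analysis: reference 85%; difference 9 points at ρ = 0.1 or 11 points at ρ = 0.5; five AR(1) measurements; 330 enrolled with 95% retained, so 330 × 0.95 / 2 = 156.75 per arm. The direction of the difference and the sidedness are not given; both directions are tried, two-sided.

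The per-arm n for two proportions at one time is multiplied by the AR(1) time-average factor Σρ^|i−j| / m². For m = 5 this is 0.2346 at ρ = 0.1 and 0.445 at ρ = 0.5.

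| Comparison | n per arm, one time | × factor, rounded up | Total N after ÷ 0.95 | Power with 330 enrolled |
|---|---|---|---|---|
| 85 v 94%, ρ = 0.1 | 181 | 43 | 91 | 99.97% |
| 85 v 76%, ρ = 0.1 | 304 | 72 | 152 | 98.6% |
| 85 v 96%, ρ = 0.5 | 111 | 50 | 106 | 99.9% |
| 85 v 74%, ρ = 0.5 | 211 | 94 | 198 | 95% |

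The stated 80% is not reproduced by this method from the stated inputs. It would need recomputing even if the logistic time-averaged test were the intended one.

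**2. Power statement and analysis side by side.**

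| Element | Power statement | Described analysis |
|---|---|---|
| Scale | proportion, 85% reference | Likert, no cut-off (Table 2) |
| Measurements | baseline, 3, 6, 9, 12 months | 3, 6, 9, 12 months (Primary Outcomes) |
| Model | logistic mixed model | latent growth curve (Planned Analytic Approach) |
| Contrast | time-averaged difference | 3-month intercept, slope, time-specific differences |

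No row agrees.

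**3. What the planned contrasts could detect (illustration).** The document gives no Likert SD or mean difference, so these are assumed: SD 1, AR(1) errors with ρ = 0.1 to 0.5, visits coded 0, 1, 2, 3, 156.75 per arm, two-sided .05, 80% power, no multiplicity correction. The detectable difference is (1.960 + 0.842) × √(2v / 156.75), where v is the per-person variance of the estimate. For the intercept and slope, v comes from generalised least squares, (X′R⁻¹X)⁻¹. For the time average, v = Σρ^|i−j| / 16.

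| Contrast | v at ρ = 0.1 | v at ρ = 0.5 | Detectable difference |
|---|---|---|---|
| Time average, four visits | 0.290 | 0.516 | 0.17 to 0.23 SD |
| 3-month intercept | 0.758 | 0.935 | 0.28 to 0.31 SD |
| Slope, per visit | 0.208 | 0.194 | 0.144 to 0.139 SD |
| Slope × 3 (months 3 to 12) | – | – | 0.43 to 0.42 SD |

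An effect just large enough to give the time average 80% power gives the intercept test 41% (ρ = 0.1) to 55% (ρ = 0.5).

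**4. Does this show low power?** Read the 9 points as a shift on a latent normal scale: Φ⁻¹(0.94) − Φ⁻¹(0.85) = 0.52 SD upward, and Φ⁻¹(0.85) − Φ⁻¹(0.76) = 0.33 SD downward. Both exceed 0.28 to 0.31 SD. For a constant difference of that size the intercept test has 86 to 99.9% power at .05, and 73 to 99.8% at .05/3. Low power is therefore not established.

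**The case against.** The strongest reply has three parts.

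First, a reader might infer that no planned test reaches 80% power. The documents do not support that. With no Likert SD or target mean difference, power cannot be computed, and on the latent-normal reading the intercept test exceeds 80% at .05. This part stands in full.

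Second, growth factors are not the only methods named. Statistical Analyses leaves methods to be chosen by hypothesis and type of measure, Planned Analytic Approach adds fixed-effect contrasts, and Missing Data adds growth mixture models. A growth model can also be fitted to a binary indicator, and a cut-off could sit in a fuller plan. So it would be wrong to say that every described test is a growth-factor contrast, or that the missing cut-off is itself an error. The mismatch remains: the fixed-effect contrasts are time-specific, none of these methods is described as a time-averaged comparison of proportions, and an unseen cut-off would not supply the baseline measurement or the time-averaged contrast.

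Third, the hypothesis that the combined intervention "will be considered acceptable, appropriate, and feasible by most participants" concerns a proportion within one arm, and a reader might infer that the plan cannot answer it. It needs only a descriptive estimate, which an article can leave to the full plan, so it is not counted as a fault.

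**Conclusion.** The power statement and the described analysis contradict each other on scale, measurements, model and contrast. The stated 80% and the 9- and 11-point differences do not apply to any described test. The actual power of the planned tests is unknown, not shown to be low.

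Under the assumptions in the working, the detectable difference runs from 0.17 to 0.23 SD for a time average, through 0.28 to 0.31 SD for the 3-month intercept, to 0.42 to 0.43 SD for divergence over the nine months of follow-up. The test to which the statement refers therefore changes the answer by about a factor of two. These figures are illustrative: they omit separate random intercepts and slopes, and the multiplicity correction promised under Statistical Analyses would raise them. That the wording conflicts rests on the text alone and needs none of these assumptions.

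**What to change.** Reconcile Sample Size Calculation and Power Analysis with Primary Outcomes, Table 2 and Planned Analytic Approach. Restate power for the planned growth-model tests, giving the detectable difference in SD units for the 3-month intercept and for the slope. State the assumed SD, correlation structure, number analysed per arm and alpha.

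If the logistic time-averaged comparison was always intended, name it, with its cut-off and measurement times, as the test to which the power statement refers, and recompute its power. Do not move the primary analysis to a newly chosen dichotomy: Results says that data collection ended in June 2024 and analysis is under way, so that would be a post-data change of primary analysis.

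Optionally, report the proportion of the uTECH+YMHP arm rating the intervention acceptable with a 95% confidence interval. At an assumed 85% and 157 raters the half-width is 1.96 × √(0.85 × 0.15 / 157) = 5.6 points (5.4 at 165, 5.7 at 150).

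The cost is a rewritten paragraph and a short recalculation. Enrolment and data collection are unaffected.

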### Target Population

This study aims to recruit 330 participants. Half (n=165, 50%) of the participants will be randomized to receive uTECH+YMHP (condition 1), and the remaining half (n=165, 50%) will be randomly assigned to receive YMHP only (condition 2).

To be eligible for the study, participants must be aged 18 to 29 years, identify as SGM, have had anal or oral sex with a man (defined by the participant’s interpretation) in the past 3 months, have used substances (such as alcohol, marijuana, amyl nitrate [poppers], methamphetamines, heroin, cocaine, and ecstasy) in the past 3 months, have had sex while using substances in the past 3 months, have a negative or unknown HIV status, and have used a dating app to meet sexual or substance use partners in the past 3 months. Participants must also own a smartphone, reside in the United States, be willing to participate in a 12-month study, and be able to provide informed consent. Participants that use an Android smartphone as their primary device must consent to install the eWellness app on their phone to remotely collect keystroke and geolocation data throughout the duration of the study. Participants who use an iOS (Apple Inc) smartphone must provide the study team with at least 1 set of data from both their primary dating app and their most-used social media account every 6 months. Failing to meet all the stated criteria would disqualify individuals from enrollment in the study. Exclusion criteria were conceived to build upon existing literature for HIV prevention in SGM populations while also expanding gender criteria to be inclusive of transgender and gender nonbinary individuals who have sex with men. Our study population aims to capture the identities of young adult users of queer-centered dating apps and websites such as Grindr, Scruff (Perry Street Software, Inc), and Sniffies (Sniffies, LLC) who may be at heightened risk of HIV and STI transmission [17-19], particularly in the context of substance use [5-9].

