### Primary Outcomes

The primary outcomes that the study will measure are the acceptability, appropriateness, and feasibility of the implementation for uTECH+YMHP and YMHP-only conditions. These primary outcomes will be assessed through surveys conducted at 3-, 6-, 9-, and 12-month time points. The study will measure how outcomes differ between uTECH+YMHP and YMHP-only conditions.

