### Statistical Analyses

Statistical methods, models, and procedures will be selected according to the research hypotheses being tested and the types of measures involved. We will set α<.05 as the level for statistical significance but will use appropriate corrections for multiple comparisons (eg, Bonferroni and Hochberg correction [73]) to ensure that the actual overall effective type 1 error remains at an α=.05 level for the tests to be conducted. The frequency and patterns of missing data will be carefully evaluated. To avoid potential bias resulting from missing data, imputation (eg, hot deck or multiple imputation [74]) will be conducted, and statistical significance tests and modeling will be conducted with and without the imputed values. The findings from these analyses will be compared, and any differences will be evaluated. Potential nonlinear relationships between continuous predictors (eg, participants’ age) and outcomes (eg, acceptability, appropriateness, and feasibility of uTECH and YMHP) will be evaluated through spline functions (eg, cubic spline).

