## Results

This study was funded in August 2019. Between August 2019 and June 2024, we have enrolled 424 participants on a rolling basis. Approximately 71% (301/424) of the study participants have completed 12 months of participation. Data collection concluded in June 2024. Data analysis is currently under way, and expected results will be published in the fall of 2025.

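### The stated detectable differences of 9% and 11% do not follow from the calculation's own inputs, which give about 5 to 6 and 7 to 8 points; its baseline measure and uncorrected alpha also disagree with the rest of the protocol

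*Protocol article*

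**What the plan says.** All of the following is in the protocol article.

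- **Target Population** gives a two-arm, 1:1 design of 330: "Half (n=165, 50%) of the participants will be randomized to receive uTECH+YMHP (condition 1"), and the other 165 to YMHP only.
- **Sample Size Calculation and Power Analysis** bases power on one primary outcome, acceptability. It uses a logistic mixed model with five measurements per person (baseline, 3, 6, 9 and 12 months) and AR(1) correlation. The inputs are "With an initial sample size of 330 (to account for 95% retention"), "a baseline effectiveness of 85"%, 80% power and alpha .05. The result at autocorrelation 0.1 is "we aimed to detect a minimum time-averaged difference of 9% in acceptability between any 2 conditions". At 0.5 it is 11%, and the text says that the sample size was altered to get there. It then states: "A 9% to 11% difference between the 2 conditions is considered statistically significant", giving as reasons the evidence for YMHP and the cost and ease of delivery of uTECH.
- **Primary Outcomes** names three outcomes (acceptability, appropriateness, feasibility) and says: "These primary outcomes will be assessed through surveys conducted at 3-, 6-, 9-, and 12-month time points". **Planned Analytic Approach** models the same four follow-ups.
- **Statistical Analyses** says the team "will use appropriate corrections for multiple comparisons (eg, Bonferroni and Hochberg correction [73"]) so that overall type 1 error stays at .05.
- **Results** reports 424 enrolled, data collection concluded, and: "Approximately 71% (301/424) of the study participants have completed 12 months of participation".

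**The concern.** The power paragraph prints nearly every input of a standard time-averaged comparison, so its two results can be checked. Five weakly correlated measures on about 157 people per arm, with a rate near 85%, should detect much less than 9 points. If the 9 and 11 are wrong, the article's only numerical benchmark for the primary comparison does not describe this design.

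Two inputs also disagree with other sections: a baseline measurement of acceptability, and an alpha with no multiplicity correction. The wording adds to the problem, because it presents a design difference as though it were a significance threshold.

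**Working it through.** **Inputs.** Two arms of 165 (Target Population). Retention 95%, so 165 × 0.95 = 156.75 per arm. Rate 85%, m = 5 measures, AR(1) with ρ = 0.1 or 0.5, alpha .05, power 80% (power section). Assumptions: alpha is two-sided, since no sidedness is given. The article does not say whether 85% is the lower or the higher of the two rates, so both directions are shown.

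**Formulas.** The variance of the mean of m AR(1) measures, relative to one measure, is

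v = [m + 2 Σ(m − k)ρᵏ] / m², with k from 1 to m − 1.

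The detectable difference d, with p₁ = 0.85 ± d, solves

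d = (z₁₋α/₂ + z₀.₈₀) × √{ v × [0.85 × 0.15 + p₁(1 − p₁)] / n }.

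| m | v at ρ = 0.1 | v at ρ = 0.5 |
|---|---|---|
| 5 | 0.2346 | 0.4450 |
| 4 | 0.2901 | 0.5156 |

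**Step 1: the article's own figure.** With n = 156.75, m = 5 and 1.960 + 0.842 = 2.802:

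| ρ | Stated | Up from 85% | Down from 85% |
|---|---|---|---|
| 0.1 | 9 | 5.05 | 5.86 |
| 0.5 | 11 | 6.73 | 8.26 |

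Check of the first cell: p₁ = 0.9005, p₁(1 − p₁) = 0.0896, and 2.802 × √[0.2346 × (0.1275 + 0.0896)/156.75] = 0.0505.

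**Step 2: power at the stated differences.** Power = Φ(d/SE − 1.960).

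| Difference | SE | Power | n per arm for 80% |
|---|---|---|---|
| 9 up, ρ = 0.1 | 0.0166 | 99.97% | 41.8 |
| 9 down, ρ = 0.1 | 0.0215 | 98.7% | 70.4 |
| 11 up, ρ = 0.5 | 0.0217 | 99.9% | 47.9 |
| 11 down, ρ = 0.5 | 0.0301 | 95.5% | 92.3 |

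**Step 3: other readings.** Working on the logit scale changes the results by only about 0.1 point. One-sided .05 lowers them further, to 4.5/5.2 and 6.1/7.3. A single time point gives about 9.5 up or 12.8 down, but the same at both autocorrelations. A change-from-baseline contrast gives 10.4/14.6 at 0.1 and 9.7/13.3 at 0.5, so it falls as ρ rises while the stated pair increases. No variant tried that keeps two arms, five AR(1) measures, .05 and 80% power returns 9 and 11.

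**Step 4: the inputs that disagree with other sections.** Acceptability is scheduled and modelled at four follow-ups, so m = 4. Three primary outcomes with familywise control at .05 give .05/3 = .0167 under Bonferroni, the strictest simple case. In each cell the first figure is upward and the second downward:

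| n per arm | Alpha | ρ = 0.1 | ρ = 0.5 |
|---|---|---|---|
| 156.75 (planned, retained) | .05 | 5.6 / 6.6 | 7.2 / 8.9 |
| 156.75 | .0167 | 6.3 / 7.7 | 8.1 / 10.5 |
| 150.5 (301 completers, even split assumed) | .0167 | 6.4 / 7.8 | 8.3 / 10.7 |
| 212 (all 424 enrolled, even split assumed) | .0167 | 5.5 / 6.5 | 7.1 / 8.9 |

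**Step 5: the significance wording.** With four measures, 156.75 per arm and both rates near 85%, the observed difference that just reaches two-sided .05 is 1.960 × √(v × 2 × 0.1275/156.75). That is 4.3 points at ρ = 0.1 and 5.7 at ρ = 0.5. A detectable difference and a significance threshold are different quantities, and neither is 9 or 11 here.

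**The case against.** The strongest reply is that the error is harmless. The stated differences are larger than 330 participants need, data collection has concluded, and no estimate or test depends on this paragraph. That is right as to consequence, and it sets the severity. It does not make the figures correct.

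Several stronger readings are tempting but not supported:

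- **Underpowering.** A reader might infer that wrong power figures mean too few participants. The error runs the other way. With four measures and the strict alpha, every case in step 4 stays below 9 and 11.
- **A decision rule.** One might infer that a real difference of 5 to 8 points would be dismissed. No section uses 9 to 11 points as a rule. Significance is set by alpha with correction, and in Mediation and Moderation by the treatment coefficients. The reasons given for the range concern practical worth, so the sentence reads as poor wording for a meaningful difference.
- **Failed retention.** The 95% was a planning assumption, and 71% is a later result. Enrolling 424 largely offset it: 301 completers against 330 × 0.95 = 313.5, about 4% fewer.
- **A leftover from a design with more arms.** The reference to any two conditions invites this, but the next sentence names the two arms. Three arms of 104.5 would give 6.1/7.3 and 8.0/10.3, which is still not 9 and 11.
- **An impossible baseline rating.** An anticipated rating after the detailed consent discussion is conceivable, and the heading over Table 2 includes baseline. What stands is the conflict with Primary Outcomes and Planned Analytic Approach. Dropping the baseline measure moves the detectable difference by about 0.5 to 0.7 points.
- **A fixed alpha of .05/3.** Bonferroni and Hochberg are given only as examples, and Hochberg can be milder. The article also says openly that one outcome was used. What remains is that the calculation and the familywise promise are not aligned.

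**Conclusion.** The concern holds in this form. On the article's own inputs, the two-arm design detects about 5.1 to 5.9 points at autocorrelation 0.1 and 6.7 to 8.3 at 0.5, where the article states 9 and 11. Power at the stated differences is about 95% to over 99.9%. This rests on a two-sided .05 and a comparison of time-averaged proportions; the spread within each range comes from the unstated role of the 85%.

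Two inputs contradict other sections: a baseline acceptability measurement outside the outcome schedule, and an uncorrected .05 for one of three primary outcomes. Aligning both raises the detectable difference, but not to the stated values. The description of 9 to 11 points as statistically significant is wrong as worded. This is a text correction that should be made. It does not cast doubt on the adequacy of the sample.

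**What to change.** Rewrite the power paragraph.

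1. Restate the detectable differences for two arms and the four post-baseline measures.
2. State as assumptions the sidedness of the test, whether 85% is the YMHP-only rate, the alpha after multiplicity correction, and the analysed sample. Imputation is planned, so completers need not be the analysed set. The table in step 4 shows the range to expect.
3. If acceptability was in fact rated at baseline, say so in Primary Outcomes and the analysis section; otherwise remove it from the calculation.
4. Replace the sentence on statistical significance with a smallest worthwhile difference, justified separately.
5. Say that at fixed N the detectable difference changes with the autocorrelation, in place of the statement that the sample size was altered.

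The cost is one paragraph and a short recalculation, with no change to enrolment, data collection or the planned tests.
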